**3.6 Sample Size Estimation**

The minimum sample size required to test the study hypotheses was calculated using the two proportions formula (Lemeshow, Hosmer, Klar, & Lwanga, 1990). The formula gave the required number (n) for each group.

2

{√2p̌ (1 − p̌) + Z1−β√p1(1 − p1) + p2(1 − p2)}

n =

(p1 − p2)2

Parameters from different intervention studies were substituted into the formula to calculate sample size as shown in Appendix H. However, a study among students by Mohammed et al. (2016) was adopted to calculate the sample size for this study.

P1 = 0.032 (proportion of students who initiated smoking among students in the intervention group after six months intervention.

P2 = 0.088 (proportion of students who initiated smoking among students in the control group after six months.

P = proportion of all subjects receiving smoking intervention after six months ((P1 +

P2)/2).

P = (0.032 + 0.088)/2 = 0.06

With Z1-α/2 = 1.96 at 95% CI and Z1-β = 1.28, at 90% power gave a minimum sample

size (n0) of 281

Adjustments were made for estimated response rates (Aday & Cornelius, 2006) thus:

i) Adjustment for estimated response rate, where the estimated attrition rate

is 20% = 337.2

This gave a sample size of 337.2 students in each group. Cluster randomized control trials are measured by design effect given as (1+ (M-1) X ICC) = 1.085.

ICC – Intra Cluster Correlation = 0.01

M – Average Cluster Size

337.2 x 1.085 (effect size of cluster random sampling) = 365.9

This gave a sample size of 366 students per group, which was then multiplied by two since the study is in two arms. Therefore, 732 is the sample required for this study.

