Tobacco use is one of the main causes of preventable deaths worldwide. Tobacco use is associated with cardiovascular diseases. There are currently about one billion smokers in the world. An estimated six trillion cigarettes are smoked annually by current smokers. Six million people die each year from tobacco use and exposure (WHO, 2011a). The GHS (2017a) reported that the prevalence of tobacco use in Ghana in 2014 was 5.1% among males and 0.4% for females. A research conducted among students of 11-17 years in Ghana revealed that prevalence of smoking among boys was 2.4% while girl smokers was 1.4% (Mamudu & Veeranki, 2013).

Alcohol consumption is associated with the risk of hypertension and hemorrhagic stroke. Globally, an estimated 3.3 million people died (5.9% of all worldwide deaths) in 2012 as a result of alcohol consumption. More than half of these deaths resulted in NCDs of which CVDs and diabetes accounted for 33% of these deaths. Globally, the levels of alcohol consumption in 2010 was estimated at 6.2 liters of pure alcohol per person ≥15 years of age (WHO, 2014). In Ghana, the levels of alcohol consumption in 2016 per person ≥15 years of age was estimated to be 2.7 liters (WHO, 2018a). In a research among 1,311 adolescents school students in Ghana found that prevalence of alcohol use among students was 42.3% (Hormenu, Hagan, & Schack, 2018).

Unhealthy diet accounts for 1.7 million deaths and 16 million DALYs worldwide as a result of low consumption of fruits and vegetables (WHO, 2014). Adequate fruits and vegetables intake reduces the risk of CVDs (Boeing et al., 2012). Consumption of high energy foods including processed foods like fats and sugars results in obesity (Mendonca et al., 2016). Also, high salt intake increases the risk of hypertension and

CVDs. Globally, the WHO has estimated that people consume between 9-12 g/day of salt which is far above the recommended intake of less than 5g/day. The WHO further indicated that saturated fat predisposes an individual to the risk of coronary heart diseases whereas monounsaturated and polyunsaturated reduces the risk (WHO, 2011a) while the consumption of fish is very low. A study in Ghana among secondary school students revealed the consumption of sweet snacks, sodas, and energy dense foods were high (Amoh & Appiah-Brempong, 2017).

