**1.6 Research Hypotheses**

The research hypotheses of this study are:

1. There will be no difference in the socio-demographic characteristics between the intervention and control groups at baseline.

2. The behavioral modification intervention program will be effective in improving the knowledge of CVD and its risk factors, motivation, and behavioral skill score among the participants in the intervention group as compared to control group and also within the groups from baseline to six months among secondary school students in Brong Ahafo, Ghana.

3. The behavioral modification intervention program will be effective in promoting physical activity levels of participants in the intervention group as compared to control group and also within the groups from baseline to six months among secondary school students in Brong Ahafo, Ghana.

4. The behavioral modification intervention program will be effective in reducing the prevalence of smoking among participants in the intervention group as compared to control group and also within the groups from baseline to six months among secondary school students in Brong Ahafo, Ghana.

5. The behavioral modification intervention program will be effective in reducing the prevalence of alcohol consumption of participants in the intervention group as compared to control group and also within the groups from baseline to six months among secondary school students in Brong Ahafo, Ghana.

6. The behavioral modification intervention program will be effective in promoting fruits and vegetable intake among participants in the intervention group as compared to control group and also within the groups from baseline to six months among secondary school students in Brong Ahafo, Ghana.

7. The behavioral modification intervention program will be effective in increasing seafood and water intake and reducing carbohydrates, fats and oils, fried eggs, fried chicken, carbonated drinks, plain sugar, sweet snack, and salted fish intake among participants in the intervention group compared to control group and also within the groups from baseline to six months among secondary school students in Brong Ahafo, Ghana.

8. The behavioral modification intervention program will be effective in reducing body weight and BMI of participants in the intervention group as compared to control group and also within the groups from baseline to six months among secondary school students in Brong Ahafo, Ghana.

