**3.16.4 Smoking**

Smoking will be categorized into ex-smokers, current smokers, and never smoker. Ever smokers were students who had ever tried smoking before but had stopped. Current smokers are those who are currently smoking tobacco. Never-smokers referred to as students who has never smoked tobacco.

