**3.17 Data Analysis**

Data collected will be collated, checked, cleaned, and analyzed using IBM Statistical Package for Social Sciences (SPSS) version 22. The data analysis will be divided into descriptive and inferential statistics. The level of significance for all the statistical tests is set at 0.05. For mean estimations, 95% confidence intervals (CI) will be computed.

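### The 90% power in section 3.6 is for six-month smoking initiation, but the trial tests smoking prevalence or status, for which the protocol's own student figures give about 25–39%

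*Protocol*

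**What the plan says.** Protocol section 3.6 presents one calculation as giving the minimum sample for testing the study hypotheses. Its inputs come from a cited school smoking-prevention trial: "P1 = 0.032 (proportion of students who initiated smoking among students in the intervention group after six months intervention" and "P2 = 0.088 (proportion of students who initiated smoking among students in the control group after six months". The error rates are given as "With Z1-α/2 = 1.96 at 95% CI and Z1-β = 1.28, at 90% power gave a minimum sample" size of 281 per group. That figure is raised by 20% for attrition to 337.2, then multiplied by a design effect ("Cluster randomized control trials are measured by design effect given as (1+ (M-1) X ICC) = 1.085") to 366 per group, 732 in total. Section 3.11 plans 848 students, 424 per arm.

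The tested quantity is described differently:
- Section 1.6, hypothesis 4: the programme will be "effective in reducing the prevalence of smoking among participants in the intervention group as compared to control group".
- Section 3.16.4: "Smoking will be categorized into ex-smokers, current smokers, and never smoker".
- Section 3.17.3: smoking status at six months is compared by chi-square between groups and McNemar within groups.
- Section 3.17: "The level of significance for all the statistical tests is set at 0.05".

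Section 1.1 gives one smoking prevalence for Ghanaian students, aged 11–17: "prevalence of smoking among boys was 2.4% while girl smokers was 1.4" per cent.

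**The concern.** A sample size supports a power claim only for the endpoint whose rates went into it. Here the rates describe starting to smoke over six months, while the hypothesis and analysis concern how many students smoke or what their smoking status is. The two quantities can differ several-fold in the same students.

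The only Ghanaian student figure in the protocol suggests that the tested rate may be low. The design difference is 8.8 − 3.2 = 5.6 percentage points. A reduction of that size cannot occur in a prevalence that starts at 1.4–2.4%.

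If the text stands, a non-significant smoking result would be read as coming from a test with 90% power. With few smokers in either arm it would be weak evidence against an effect.

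**Working it through.** **Inputs.** p1 = 0.032, p2 = 0.088, z = 1.96 and 1.28, design effect 1.085, attrition 20% (all section 3.6); 424 per arm (section 3.11); student prevalence 1.4% and 2.4% (section 1.1). Three inputs are assumed: the risk ratio of section 3.6 carries over, 0.032/0.088 = 0.364; 1.9% serves as a midpoint; and 5.1%, the general-population male tobacco-use figure in section 1.1, serves as an upper case.

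**1. The plan's own figure.** The pooled two-proportion formula is

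n = {1.96·√[2p̄(1−p̄)] + z_β·√[p1(1−p1) + p2(1−p2)]}² / (p1−p2)².

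With p̄ = 0.06 the two roots are √0.1128 = 0.3359 and √0.111232 = 0.3335.
- z_β = 1.28 (90% power): (0.6583 + 0.4269)² / 0.003136 = 375.5, so 376 per group.
- z_β = 0.84 (80% power): (0.6583 + 0.2802)² / 0.003136 = 280.8, so 281 per group.

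The printed 281 corresponds to 80% power, not 90%. The later steps do reproduce: 281 × 1.2 = 337.2, × 1.085 = 365.9, so 366 per group. The larger planned enrolment partly repairs this for initiation. With 424 per arm and design effect 1.085, power for 3.2% against 8.8% is 91% without losses and 84% after 20% loss.

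**2. Power for prevalence at the protocol's student rates.** The effective number per arm is 424/1.085 = 390.8, with square root 19.77. Power is Φ(z), where

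z = {|p1−p2|·√n − 1.96·√[2p̄(1−p̄)]} / √[p1(1−p1) + p2(1−p2)].

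Worked example at a control rate of 1.9%: p1 = 0.019 × 0.364 = 0.0069 and the difference is 0.0121, so z = (0.0121 × 19.77 − 1.96 × 0.1599)/0.1597 = −0.47 and power is 32%.

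| Control rate | Intervention rate | Power, no loss | Power, 20% loss |
|---|---|---|---|
| 1.4% | 0.51% | 25% | 21% |
| 1.9% | 0.69% | 32% | 27% |
| 2.4% | 0.87% | 39% | 32% |
| 5.1% | 1.85% | 70% | 60% |

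**3. Checks on scale.**
- Expected smokers in a control arm of 424: 424 × 0.014 = 5.9 to 424 × 0.024 = 10.2.
- Complete elimination of smoking in the intervention arm (design effect 1.085, no loss) would be detected with about 65%, 78% and 87% power at 1.4%, 1.9% and 2.4%.
- The number per arm for 90% power at the same risk ratio, before attrition and clustering, would be 2502, 1837 and 1449.

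**The case against.** **The prevalence figure may not fit these students.** It is national, for ages 11–17. The trial's students are 14–19 (section 3.1) and come from two districts. The protocol does not say how that source defined smoking, and it gives no rate for ever-smoking, which the status variable also captures. Section 2.6.2 gives 10% for Ghana as a whole. At that rate the same formula gives z = (0.0636 × 19.77 − 1.96 × 0.3565)/0.3536 = 1.58, about 94% power. This stands as a limit on precision: 25–39% is conditional on an assumed rate. The 5.1% and 10% figures are not student data, though, and 3.6 uses none of these rates.

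**Initiation can be derived.** Questionnaire item 30 asks about ever having tried a cigarette, status is collected at both time points, and not starting to smoke is an aim of the intervention. It would therefore be wrong to infer that the trial cannot study initiation. What remains is that the protocol does not name it as the tested outcome.

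**The rates do not contradict each other.** A reader might infer that 8.8% is refuted by 1.4–2.4%. One is new uptake over six months and the other a prevalence. If uptake includes experimenters, it can exceed current smoking.

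**Other outcomes may be sized elsewhere.** A reader might infer that the sample is unsupported for every hypothesis. Section 3.6 says that parameters from several studies were tried and refers to Appendix H, which is not in the available text. Smoking is also one of seven listed primary outcomes. The point is confined to smoking.

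**Neighbouring issues are not used here.** Whether 1.085 suits four large schools is a separate question about clustering; the figures above use the protocol's own value. Whether McNemar's test suits a three-level status has no bearing on sample size.

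**Conclusion.** The mismatch is plain in the text and depends on no assumption: section 3.6 sizes on initiation, while hypothesis 4 and sections 3.16.4 and 3.17.3 test prevalence or status. The stated 90% is therefore not a power for the smoking outcome tested.

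The size of the shortfall does depend on assumptions: the control rate, the carried-over risk ratio of 0.36, 424 per arm without losses, and the design effect of 1.085. On the protocol's student prevalence, power is about 25–39%; at 5.1% it is about 70%. A well-supported higher control rate would raise these figures, but the protocol offers none for Ghanaian students. The conclusion does not extend to the other primary outcomes.

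**What to change.** 1. Use one binary smoking endpoint for both sizing and analysis. Either of these would do:
   - current smoking, yes or no, in all enrolled students; or
   - initiation by six months among baseline never-smokers, from item 30. Only never-smokers then count towards the sample, so the calculation must allow for the smaller denominator.
2. Word hypothesis 4 and sections 3.16.4 and 3.17.3 to match. The three-level status table can stay as description.
3. Recompute section 3.6 with a control rate justified for that endpoint in Ghanaian students, and state the resulting power for smoking. Correct the pairing of 281 with 90% power at the same time.
4. Limit the statement that the calculation serves the study hypotheses to those outcomes whose calculations, including any in Appendix H, support it.

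The cost is a recalculation and rewording. The drawback is that the stated power for smoking is likely to look much less favourable. No change in enrolment is needed to make the correction.

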**3.2 Study Design**

This study is a two arm single blind parallel cluster randomized controlled trial involving four public secondary school students that will be recruited into the study from two selected districts in Brong Ahafo region and will be guided by the CONSORT statement (Moher et al., 2010). Schools will be the unit of randomization, intervention, and analysis. Respondents in the intervention arm will receive CVD behavioral modification intervention based on the IMB model, whereas the control group will not be exposed to the intervention but will go on with their normal school curricula. Students in the control group will be wait listed and will receive the intervention program at the end of the study. Baseline measurements of CVD knowledge and its risk factors, motivation, behavioural skills, physical activity, smoking, alcohol consumption, dietary intake, body weight, height, diastolic and systolic BP will be taken for both the intervention and control groups. A post intervention assessment will then be carried out within two weeks immediately after six months to evaluate the effectiveness of the intervention.

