**3.7 Randomization**

Randomization technique in the ratio 1:1 for intervention and control groups respectively will be carried out. Public secondary schools (clusters) will be the unit of randomization. Schools (students) will be randomly assigned to either the intervention or control group of the study on the same day participants will be selected for this study. It will however be performed after baseline data has been collected.

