**3.7.1 Sequence Generation**

A biostatistician who will not be involved in the trial will generate the allocation sequence. Using a block randomization (1:1 ratio) of two digit blocks A and B (each containing one intervention and one control, to ensure equal distributions in the two groups will be used), two schools each will be allocated to intervention and control groups.

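### Section 3.6 claims 90% power from a student-level normal formula; if school is the unit of analysis, as Section 3.2 says, two schools per arm leave 2 degrees of freedom and about 21% power

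*Protocol*

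**What the plan says.** Section 3.6 states that the required number was "calculated using the two proportions formula", with smoking initiation of 0.032 (intervention) and 0.088 (control). It continues: "With Z1-α/2 = 1.96 at 95% CI and Z1-β = 1.28, at 90% power gave a minimum sample" size of 281 per group. That figure is raised to 337.2 for 20% attrition and multiplied by a design effect of 1.085 (ICC 0.01), giving 366 per group and 732 in all. Section 3.11 plans 848 students, 424 per arm.

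Section 3.2 states: "Schools will be the unit of randomization, intervention, and analysis". Section 3.7.1 states that "two schools each will be allocated to intervention and control groups", using two blocks that each hold one intervention and one control school.

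Section 3.17.3 lists chi-square and McNemar tests for smoking and alcohol, t-tests, a mixed-design ANOVA and a GLMM. It names no school-level comparison and no term for school.

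**The concern.** The quantiles 1.96 and 1.28 suit a standard error estimated from many independent units. With school as the unit there are four, and the variation between schools within an arm has to be estimated from two schools in each arm. A design effect enlarges the variance but leaves the normal quantiles in place, so correcting its cluster size does not cure this.

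At stake is how the result will be read. If the chance of detecting the target effect is nearer one in five than nine in ten, a non-significant difference says little, yet the printed 90% invites reading it as evidence against the programme. At ICC 0.01, recruiting more students in the same four schools cannot close the gap.

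**Working it through.** **Inputs.** P1 = 0.032, P2 = 0.088, mean 0.06, two-sided 5%, ICC 0.01, 20% attrition (Section 3.6); two schools per arm (Section 3.7.1); 424 students per arm (Section 3.11), so 212 per school, or 366 per arm (Section 3.6), so 183 per school.

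**1. The plan's own figure.** n = {1.96·√(2·0.06·0.94) + Z·√(0.032·0.968 + 0.088·0.912)}² / 0.056² = {0.6583 + Z·0.3335}² / 0.003136.
- Z = 1.28 (90%): 375.5 per group.
- Z = 0.84 (80%): 280.8 per group.

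The printed 281 therefore matches the student-level formula at 80% power, not 90%. The later steps reproduce: 281 × 1.2 = 337.2 and 337.2 × 1.085 = 365.9. A design effect of 1.085 at ICC 0.01 implies a cluster size of 9.5, whereas four schools supplying 732 to 848 students means 183 to 212 each. Both are separate errors in the same section.

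**2. School-level comparison, unpaired.** Degrees of freedom are 2(2 − 1) = 2, and the two-sided 5% critical value is 4.303.
- Design effect: DE = 1 + (m − 1)·ICC, with m students per school.
- Standard error: SE = √(0.111232·DE / n per arm), where 0.111232 = 0.032·0.968 + 0.088·0.912.
- Noncentrality: 0.056/SE.

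At 424 per arm and ICC 0.01, DE = 1 + 211·0.01 = 3.11, SE = 0.02856 and noncentrality = 1.96.

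| Case | Noncentrality | Normal formula, same SE | t, 2 df |
|---|---|---|---|
| ICC 0.01, 848 students | 1.96 | 50% | 21% |
| ICC 0.01, 732 students | 1.91 | 48% | 20.5% |
| ICC 0.01, 848 less 20% attrition (339.2 per arm) | 1.89 | 47% | 20% |
| ICC 0, 848 students | 3.46 | 93% | 47% |
| ICC 0, 732 students | 3.21 | 89% | 43% |
| ICC 0.01, unlimited students per school | 2.37 | 66% | 28% |

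For the last row, SE tends to √(0.111232·0.01/2) = 0.02358.

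**3. Simulation check.** A t-test on the four school proportions (beta-binomial at ICC 0.01) gave 23% at 848 students, 22-23% at 732 and 30% with 100,000 students per school. With independent students (ICC 0) it gave 49% at 848 and 44% at 732. Rejection under no difference (6% vs 6%) was 5.0%.

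**4. Blocks analysed as pairs.** Two pairs leave 1 degree of freedom (critical value 12.71). With the same SE at 848 students, power is about 12% at ICC 0.01 and 21% at ICC 0.

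**The case against.** The strongest reply is that the 2-df test is inferred. Only one sentence, in Section 3.2, makes school the unit of analysis. Section 3.17.3, where the tests are listed, names none at school level, and tests on students would not use 2 df. This stands: the power figures hold only if Section 3.2 governs, and the protocol contradicts itself on the point. It does not rescue the 90%. Tests that treat students as independent would understate the standard error, by a variance factor of about 3.1 at the protocol's ICC and 212 per school. A mixed model that does include school still has only four schools from which to judge variation between schools.

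Three stronger readings are tempting and are not supported.

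- A reader might put the whole fall from 90% to 21% down to degrees of freedom. That part is only the step from about 50% to about 21%. The understated design effect and the 281 that matches 80% power are separate.
- A reader might infer that power fails outright even without clustering. At ICC 0 students are independent and a student-level test at 848 would have about 93% power; the 47% arises only if the data are reduced to four school results.
- A reader might multiply the noncentrality needed for 90% power (6.80) by the SE above and quote a detectable difference of about 19 points. That SE belongs to 3.2% vs 8.8% and changes with the proportions, and no reduction from 8.8% can reach 19 points.

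Nor is 2 df printed in the protocol. It follows from two schools per arm compared without pairing, and the paired reading is less favourable. The degrees-of-freedom method for a mixed model may properly sit in an analysis plan that is not shown. The formula, quantiles, power claim and unit of analysis are all stated in the protocol.

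**Conclusion.** The point holds, conditionally. If school is the unit of analysis, Section 3.6 uses the reference distribution of a different test. The protocol's target effect would then have about 21% power at 848 students before attrition, and about 20% at 732 or after 20% attrition, against a stated 90%. At ICC 0.01 the ceiling is about 28-30% with four schools; the best case, ICC 0, is about 47%.

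These figures assume an unpaired comparison on 2 df, equal school sizes and the protocol's own proportions and ICC. The 21% is one scenario rather than a figure the protocol fixes, since pairing by block would give about 12%. Because Section 3.6 does not support 90% power under a school-level analysis, or under a student-level one that ignores school, it must be corrected.

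**What to change.** 1. Reconcile Section 3.2 with Section 3.17.3 so that one stated analysis accounts for school, and say whether the two randomization blocks are analysed as pairs.
2. In Section 3.6, replace the 90% claim with the power of that analysis, using t quantiles on the cluster-level degrees of freedom. For the unpaired case this is about 21% at 3.2% vs 8.8%, ICC 0.01 and 848 students. Print beside it the ICC 0 case (about 47%) and the ceiling of about 28-30% with four schools.
3. State that a non-significant difference is not evidence of no effect.

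The cost is rewording of Sections 3.2, 3.6 and 3.17.3, with no extra schools, students or data. The downside is a much less favourable printed power.

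### Section 3.6 claims 90% power, but its inputs then require 376 students per group; the stated 281 is the 80%-power figure, and the uplift for 20% attrition is also too small

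*Protocol*

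**What the plan says.** Section 3.6 (Sample Size Estimation) bases the sample size on smoking initiation at six months. It uses the two-proportion formula with inputs from one earlier school trial: "P1 = 0.032 (proportion of students who initiated smoking among students in the intervention" group, "P2 = 0.088 (proportion of students who initiated smoking among students in the control" group, and the average "P = (0.032 + 0.088)/2 = 0.06". The error rates are set by "With Z1-α/2 = 1.96 at 95% CI and Z1-β = 1.28, at 90% power gave a minimum sample" size of 281 per group. The two-sided 1.96 agrees with section 3.17, where "The level of significance for all the statistical tests is set at 0.05".

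The section then allows for 20% attrition: "This gave a sample size of 337.2 students in each group". It multiplies by a design effect of 1.085 (with ICC 0.01) to reach 365.9, rounds to 366 per group and doubles to 732. The abstract and section 3.11 plan 848 students, 424 per arm. Section 3.5.2 starts from a list of 950 students in four schools.

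**The concern.** The power target is stated twice, as 90% and as 1.28, and the two agree with each other. The result, 281, does not follow from them. The attrition step also fails on its own terms: 20% of 337.2 lost leaves fewer students than the minimum it was meant to protect.

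This is the only sample-size justification in the protocol, and it is presented as the number needed to test the study hypotheses. If it stands, an ethics committee approves the trial on a power it does not have, and a null smoking result would later be read as if the trial had 90% power to detect the assumed difference.

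**Working it through.** **Inputs, all from section 3.6:** p1 = 0.032; p2 = 0.088; p̄ = 0.06; difference 0.056; Z(1-α/2) = 1.96; Z(1-β) = 1.28; attrition 20%; design effect 1.085; ICC 0.01. Planned enrolment of 848 is from section 3.11, and four schools from section 3.2.

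**Formula:** n = [Z(1-α/2)·√(2p̄(1−p̄)) + Z(1-β)·√(p1(1−p1) + p2(1−p2))]² / (p1−p2)²

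- √(2 × 0.06 × 0.94) = √0.1128 = 0.33586
- √(0.032 × 0.968 + 0.088 × 0.912) = √0.111232 = 0.33352
- (p1−p2)² = 0.003136

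**Reproducing 281.** With Z(1-β) = 0.84: (0.6583 + 0.2802)² / 0.003136 = 280.8, so 281. The power at n = 281 is 79.98%.

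**With the stated 1.28:** (0.6583 + 0.4269)² / 0.003136 = 375.5, so 376.

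**Other formula variants at 90% power, per group:**

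| Variant | n |
|---|---|
| Unpooled variance | 372 |
| Pooled variance throughout | 378 |
| Continuity correction | 411 |
| One-sided | 307 |
| Arcsine, two-sided | 357 |
| Arcsine, one-sided | 291 |

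None comes within 3% of 281. The formula as it appears in the text lacks Z(1-α/2) before the first root. That may be a loss in reading the PDF and is not counted as an error. Leaving the term out would give about 186, so it does not explain 281.

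**Attrition:**

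- Plan: 281 × 1.2 = 337.2. After 20% loss: 337.2 × 0.8 = 269.8, below 281.
- Needed: 281 / 0.8 = 351.25, so 352.

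**Later steps.** 337.2 × 1.085 = 365.9 and 2 × 366 = 732 are carried out correctly, but they start from the figures above.

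**Totals with the protocol's design effect of 1.085:**

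| Change | Per arm | Total |
|---|---|---|
| As stated | 366 | 732 |
| Attrition corrected only: 281/0.8 × 1.085 | 382 | 764 |
| Power corrected only: 376 × 1.2 × 1.085 | 490 | 980 |
| Both: 376/0.8 × 1.085 | 510 | 1,020 |

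**Power after 20% loss,** from Φ{[0.056·√n − 1.96 × 0.33586] / 0.33352}, where n is the effective number per arm:

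- 732 enrolled: 366 × 0.8 / 1.085 = 269.9, power 78%.
- 848 enrolled: 424 × 0.8 / 1.085 = 312.6, power 84%.

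**Dependence on the design effect.** With ICC 0.01, a design effect of 1.085 implies a cluster size of 1 + 0.085/0.01 = 9.5. Four schools sharing 848 students average 212, which gives 1 + 211 × 0.01 = 3.11. After 20% loss each school has 169.6 students and the design effect is 2.686. The effective number is then 339.2 / 2.686 = 126.3 per arm and power is about 47%. Keeping 3.11 after the loss gives 109.1 per arm and 41%.

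**The case against.** The strongest case on the other side concerns size and remedy, because the mismatch itself cannot be argued away. Appendix H is cited for calculations from other studies and is not in the text at hand. It could not help, since section 3.6 states both the inputs it adopted and the result they gave.

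Four points deserve a fair answer.

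- **Attrition.** Multiplying by 1.2 is a common approximation and it moves the number upward. A reader might infer that the adjustment runs in the wrong direction. It does not; it is too small, by about 14 students per group before the design effect. Alone it moves 732 to 764, which 848 already exceeds. It is the lesser error.
- **Enrolment is 848, not 732.** This stands in part. With 848, a design effect of 1.085 and no losses, power is about 91%. But the protocol itself expects 20% loss, and then 84% is the figure. The 1,020 needed for 90% exceeds even the initial list of 950.
- **Which entry is the slip?** A reader might infer that 80% was the intended target. The document does not show this: 90% and 1.28 agree, and 281 is the outlier. The authors must reconcile the two openly.
- **Is relabelling enough?** A reader might infer that calling 281 the 80% figure settles the matter, since 764 is below 848 and no further enrolment would be needed. The protocol does not support that. It holds only with the design effect of 1.085, which does not fit four schools of this size. It would replace one unsupported power statement with another.

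**Conclusion.** The 90% power statement in section 3.6 is wrong as written. The stated inputs need 376 per group, and 281 is about 25% below that (281/375.5 = 0.75). It corresponds to 80% power under individual randomisation. The attrition uplift is a second, smaller error (337.2 instead of 351.25). Together they put 732 about 28% below the 1,020 that 90% power would require.

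The 1,020, 78% and 84% all rest on the protocol's smoking rates, a full 20% loss and the design effect of 1.085 taken at face value. They show the effect of these two errors alone and are not the power this trial will have. On the protocol's own ICC and number of schools, the power of 848 after 20% loss is roughly 47%. The design effect is a separate defect and a larger one, but the restated power cannot be final until it is put right.

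**What to change.** In section 3.6:

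1. Delete the claim that 281 gives 90% power. Either show n0 = 281 as the 80%-power figure (Z(1-β) = 0.84) before clustering, declared as the target, or show n0 = 376 for 90%.
2. Inflate for attrition by 1/(1 − 0.20): 281 becomes 352, or 376 becomes 470.
3. Carry the chosen figure through the remaining steps with a design effect that matches the actual number of students per school.
4. State the power that the planned 848 deliver after 20% loss under that design effect. Do not state that 848 secures 80% power or that enrolment is adequate unless that calculation shows it.

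The correction itself costs a few lines of text and no new data. The stated power will become less favourable. Whether the design then needs to change depends on the corrected design effect, and these two corrections do not settle it.
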